## Abstract

**Background:**

One of the crucial challenges for the future of therapeutic approaches to Alzheimer’s disease (AD) is to target the main pathological processes responsible for disability and dependency. However, a progressive cognitive impairment occurring after the age of 70, the main population affected by dementia, is often related to mixed lesions of neurodegenerative and vascular origins. Whereas young patients are mostly affected by pure lesions, ageing favours the occurrence of co-lesions of AD, cerebrovascular disease (CVD) and Lewy body dementia (LBD). Most of clinical studies report on functional and clinical disabilities in patients with presumed pure pathologies. But, the weight of co-morbid processes involved in the transition from an independent functional status to disability in the elderly with co-lesions still remains to be elucidated. Neuropathological examination often performed at late stages cannot answer this question at mild or moderate stages of cognitive disorders. Brain MRI, Single Photon Emission Computed Tomography (SPECT) with DaTscan®, amyloid Positron Emission Tomography (PET) and CerebroSpinal Fluid (CSF) AD biomarkers routinely help in performing the diagnosis of underlying lesions. The combination of these measures seems to be of incremental value for the diagnosis of mixed profiles of AD, CVD and LBD. The aim is to determine the clinical, neuropsychological, neuroradiological and biological features the most predictive of cognitive, behavioral and functional impairment at 2 years in patients with co-existing lesions.

**Methods:**

A multicentre and prospective cohort study with clinical, neuro-imaging and biological markers assessment will recruit 214 patients over 70 years old with a cognitive disorder of AD, cerebrovascular and Lewy body type or with coexisting lesions of two or three of these pathologies and fulfilling the diagnostic criteria for dementia at a mild to moderate stage. Patients will be followed every 6 months (clinical, neuropsychological and imaging examination and collection of cognitive, behavioural and functional impairment) for 24 months.

**Discussion:**

This study aims at identifying the best combination of markers (clinical, neuropsychological, MRI, SPECT-DaTscan®, PET and CSF) to predict disability progression in elderly patients presenting coexisting patterns.

**Trial registration:**

NCT02052947.

## Background

Whereas young patients presenting a neurocognitive disorder are mostly affected by pure lesions related to Alzheimer’s Disease (AD), Vascular Dementia (VaD) that may be induced by CerebroVascular Disease (CVD) or Lewy Body Dementia (LBD), ageing favours the occurrence of co-lesions of these pathologies (Fig. 1). Age is the strongest risk factor for dementia [1]. As the populations of Western countries age, the incidence and prevalence of dementia will rise significantly. The exponential relationship between age and the prevalence of dementia, combined with the increasing number of people surviving into old age, is driving the prevalence of AD and related diseases upward, particularly LBD and CVD.

**Fig. 1 Fig1:**
[figure not shown]
Aging and the co-occurrence of Alzheimer, vascular and Lewy types

AD, the most frequent neurodegenerative aetiology of neurocognitive disorders, is marked pathologically by plaques composed of ß amyloid deposits (Aß) surrounded by dystrophic neuritis, neurofibrillary tangles composed of hyperphosphorylated tau, with activated microglia and reactive astrocytes, neuronal and synaptic loss. These lesions lead to neural loss and brain atrophy [2]. Amnestic presentation including impairment of learning and recall of recently learned information is the most common syndromic presentation of AD at the mild cognitive stage [3], latterly combined with aphasia, agnosia, apraxia and executive function impairment, some functional decline and behavioural disorders at the dementia stage [4].

LBD is marked by fluctuating cognitive decline, sleep neuropsychiatric disorders, early well-formed hallucinations, parkinsonism, and other supportive features such as dysautonomy and high sensitivity to antipsychotics [5].

CVD is the second or third most common cause of neurocognitive disorder, often associated to other pathological processes contributing to cognitive decline. Clinical symptoms depend on the location of the vascular lesions. Different CVD must be considered, i.e. multi-infarct dementia, post-stroke dementia and subcortical ischemic vascular disease [6]. Combined to clinical signs and symptoms, brain MRI is the imaging method of choice for in vivo assessment of CVD [7].

Numerous studies describe the clinical features and course of “pure” AD, in particular, the relationship between the cognitive status, behavioural disorder and the functional decline. Patients with the greatest decrease in cognitive function with respective average annual rates of decline in the Mini Mental State Examination (MMSE) show the highest decrease in score for the Instrumental Activities of Daily Living (IADL) scale as well as the most severe behavioural disturbance [8]. Far fewer data are available for VaD and AD+CVD, despite their high prevalence [9]. Patients with VaD, AD+CVD, and AD present different features at baseline and during follow-up, what underlines the need to be distinguished between them. Few studies have followed CVD or AD+CVD patients longitudinally to assess the course of their cognitive decline. Such studies have also produced conflicting results [10–12]. With regard to AD and LBD, the study of Schneider et al. had shown that a large majority of the older persons with LBD and dementia had coexisting AD pathology [13] and according to Nelson et al., the clinical diagnoses of LBD and LBD + AD were suboptimal when contrasted with autopsy results [14], which makes the assessment of cognitive status, behavioural disorder and functional decline in these underlying lesions difficult.

The aim of this study is to identify the markers, as assessed by Magnetic Resonance Imaging (MRI), Single Photon Emission Computed Tomography (SPECT-DaTscan®), Positron Emission Tomography (PET) and CerebroSpinal Fluid (CSF), combined with clinical information, that are the most predictive of functional disability progression in the elderly presenting a progressive cognitive decline related to AD, LBD, CVD and all mixed patterns. This approach will allow better defining the therapeutic targets in the elderly at a medium term.

## Methods and design

### Study aims

#### Principal objective

To identify imaging markers illustrating co-lesions of Alzheimer’s, cerebrovascular and Lewy body types of dementia the most predictive of functional disability progression.

#### Secondary objectives

To identify a combination of clinical and blood markers, in addition to imaging markers, the most predictive of functional disability progression,To identify, in a subgroup, a combination of CSF markers, in addition to clinical/blood and imaging markers, the most predictive of functional disability progression,To identify clinical/blood, imaging and CSF markers the most predictive of the cognitive decline and neuropsychiatric symptoms,To evaluate the relationship between imaging and CSF markers related to co-lesions (AD, CVD and LBD) and neuropsychological performance,To identify, in AD, AD+CVD and LBD patients, the links between neuro-imaging, biological and clinical markers on the one hand, and the response to AD specific treatments on the other hand.To evaluate the relationship between amyloid deposition and co-lesions on the one hand, and the relationship between amyloid PET imaging markers and cognitive performances on the other.

### Study design

Multicentre and prospective cohort study with 214 patients enrolled with pathology of AD, CVD or LBD or with clinical, neuroimaging and biological markers suggesting coexisting lesions of these three pathologies and fulfilling the diagnostic criteria for dementia at a mild to moderate stage.

### Setting

The study is being conducted in 8 centres: 7 French national memory centres (Paris (AP-HP), Poitiers, Tours, Strasbourg, Grenoble, and 2 in Lyon) and 1 in the Monaco Principality.

### Characteristics of participants

#### Inclusion criteria

Male or female subjects aged over 70 yearsOut-patient consulting at one of the Memory Centres participating in the studyPatients meeting diagnosis criteria for dementia due to Alzheimer (McKhann, Knopman et al. 2011), cerebrovascular (NINCDS–AIREN criteria, Roma’n, G. C., Tatemichi, T. K., Erkinjuntti, T., et al. (1993), or Lewy body type (McKeith, Dickson et al. 2005), and patients presenting mixed signs and symptoms suggesting a combination of these diagnosesMild or moderate dementia stage (MMSE criteria > 15)Being covered by health insurancePatients with sufficient visual, auditory and oral and written French language skills to complete the clinical and neuropsychological evaluationsAccompanied by a close relation in sufficient contact with the subject to assess their dependency

#### Non-inclusion criteria

Patients with psychiatric disorders (Axe 1 DSMIV disease) excepting patients with depressive or anxious disorders stabilized for more than 3 monthsPatients taking any neuroleptic psychotropic medicationPatients taking other psychotropic medication, with the exception of any antidepressant, hypnotic, anxiolytic, acetylcholinesterase inhibitors or memantine which has been prescribed and stabilised for more than 3 monthsPatients with signs and symptoms suggestive of dementia related to diseases other than AD, CVD and LBD or mixed formsPatients with other neurological diseasesPatients with progressive and unstable pathologies which could interfere with the variables under considerationDeafness or blindness which could compromise evaluation of the patientPatients being not able to undergo DaTscan®: with moderate or severe hepatic or renal impairment, a known hypersensitivity to ioflupane or any of the excipientsIf amyloid PET accepted: Patients not being able to undergo Florbetapir: with moderate or severe hepatic or renal impairment, a known hypersensitivityPatients living in an institutionPatients meeting brain MRI exclusion criteria (pacemakers, aneurysm clips, artificial heart valves, ear implants, metal fragments or foreign objects in the eyes, skin, or body) or refusing MRIPatients being under guardianship

### Measures

All measures are reported in Table 1.

**Table 1 Tab1:** Typical schedule for a patient enrolled in the CLEM protocol: summary of different stages

	Baseline	Month 6	Month 12	Month 18	Month 24
Consent	✓				
Inclusion/non inclusion criteria	✓				
Medical history or event	✓	✓	✓	✓	✓
Clinical examination	✓	✓	✓	✓	✓
CDR	✓		✓		✓
DAD	✓	✓	✓	✓	✓
IADL	✓	✓	✓	✓	✓
MMSE	✓		✓		✓
Neuropsychological diagnosis testing	✓				
ADAS-Cog/BREF	✓		✓		✓
NPI	✓	✓	✓	✓	✓
Medication	✓	✓	✓	✓	✓
Blood sampling	✓				
Neurobiotec Biobank	✓				
MRI	✓				
SPECT-DaTscan®	✓				
Amyloid PET	✓				
LP (optional)	✓				

#### Timeline

Start of recruitment: January 2014.

Duration of the recruitment period: 4.5 years.

Duration of individual participation: 2 years.

Final data collection date for primary outcome measure: July 2018.

End of the study: October 2020.

#### Outcome measures

The primary endpoint is based on the dependency progression at 2 years defined by the Disability Assessment for Dementia (DAD) scale.

#### Neuropsychological tests: Performances assessments

This assessment is included in the usual clinical practice. These tests will take place in the presence of a neuropsychologist. Besides the clinical evaluation and the initial neuropsychological inventory adapted to each team’s habits to obtain a Clinical Dementia Rating (CDR) value, all subjects will also undergo:➢ For the diagnosis and correlation with imaging and CSF markers: MMSE [15] for global cognition, 16-item Free and Cued Recall Test (FCRT) to evaluate verbal episodic memory [16], Grober and Buschke [17] to evaluate visual recognition memory, Delayed Matching-to-Sample (DMS 48) [18] to evaluate visual recognition memory, DO80 [19] and Bachy-Langedock denomination task (Bachy-Langedock 1989) to evaluate language, Verbal fluency (letter P and category: animal in 2 min) [20], Working memory and executive functions with Wechsler Adult Intelligence Scale span digit test (Wechsler 1981), Trail Making test [21] and Stroop Test [22] to evaluate executive function, Visual Object and Space, Visuospatial, and visuo-perceptive abilities were studied, Perception battery [23], and Praxes and meaningless gestures comprehension test [24].➢ For longitudinal assessments: MMSE, BREF [25] and Adas-Cog [26] to assess quantification of cognitive function.

#### MRI: Parameters studied and sequences

This acquisition is included in the clinical usual practice and will be performed on 3 T MRI in all centres.

A morphologic MRI will be performed as part of the battery of exploratory tests habitually carried out when a patient presents with degenerative cognitive disorders on diagnosis.

Parameters studied will be brain volume, ventricular volume, regional cortical volume, hippocampal volume, ischemic vascular lesions and microbleeds.

These analyses will perform on:1 mm isotropic 3D T1 sequences without contrast injection for the quantification of Brain Parenchymal Fraction and VentriclesT2 gradient echo sequence, for the detection of microbleeds and amyloid angiopathy1 mm isotropic 3D FLAIR sequence (only for 3 T) or 3 mm axial 2DFLAIR (1.5 T), for the quantification of vascular and bright objectsDiffusion (b = 1000) with ADC cartography, for silent infarcts

Processing of MRI data will be performed by the “Centre d’Acquisition et de Traitement Automatisé des Images” (CATI, Head: [name], Orsay). Quality control at the different steps of MRI data acquisition will be made.

#### SPECT: DaTscan® product and acquisition

Image acquisition and reconstruction will be performed with a SPECT/CT device, equipped with low-energy high-resolution (LEHR) parallel arrays, 3 h after intravenous injection of 111 to 185 MBq of 123I-FP-CIT and after oral administration of 400 mg of potassium perchlorate for thyroid uptake freezing. This exam will be conducted under the same conditions as the usual clinical practice. DaTscan (^123^I-Ioflupane Injection) is a radiopharmaceutical indicated for striatal dopamine transporter visualization using SPECT.

The acquisition parameters are standardized and will last 30 min. Quality control and processing of SPECT data will be performed by the CATI.

#### Amyloid PET: Product and acquisition

The acquisition of the PET image will start about from 30 to 50 min after intravenous injection of Florbetapir and will last 10 min. Patients must be lying on the back, head positioned so that the brain, including the cerebellum, are at centre of the field of view of the camera. It will be necessary to limit the movements of the head using adhesive strips or any flexible contention to maintain the head. The reconstruction should include a correction in order to obtain a size of pixels between 2.0 and 3.0 mm for axial images.

Florbetapir is a tracer indicated for PET imaging to estimate the density of beta amyloid plaques in the brain of adult patients with cognitive decline who are under evaluation for AD and other causes of cognitive impairment.

All data will be analysed by the CERMEP which is an in vivo multimodal dedicated to basic research and clinical imaging centre, in Lyon.

#### LP: Biomarkers

All collected samples will be sent to a central biobank for storage (Neurobiotec bank). Any use of the blood biobank will need to be approved by the study co-coordinators and the scientific committee.

The LP will follow the guidelines published in 2011 [27].

The CSF biomarkers will be determined in duplicates using standardized, commercially available ELISA Kits (Innotest β-amyloid 1–42, Tau, and Phospho-Tau (181P), Innogenetics, Ghent, Belgium). The samples will be analysed with the same batch of assay kits to decrease variability inter-lots of production of ELISA kits.

The biomarkers t-Tau, p-Tau, Aβ1–42, Aβ1–40, Total tau (t-tau),181 Phosphorylated tau (p-tau) and a-syn will be measured. If needed and depending upon the data obtained with these 3 first biomarkers, Aβ1–40 will be also measured.

### Data collection procedures

The anonymity of patients will ensure the following will be reported on the Case Report Form (CRF): the first letter of the name and surname, the number of patient inclusion corresponding to order number and the number of centre.

For each patient included in the study, case report forms anonymized includes the following informations: information to help guide the data collection, inclusion and non-inclusion Criteria to validate, patient Characteristics, clinical data, neuropsychological tests, blood sampling, MRI results, SPECT-DaTscan® results, Amyloid PET results, LP results, serious Adverse Events and withdrawal from study.

Each of these informations will exist in duplicate. Investigators will retain the duplicate, and will give the original to the Clinical Research Associate (CRA) monitor. CRF will be kept in the patient’s medical records by the investigator during the study. For each patient, the CRA will centralize slips and links and archive them. The number of inclusion will be present on each sheet of the CRF. This number of inclusion will be used to connect the various slips of the same patient. At each inclusion or withdrawal from study, the medical investigator will notify the Coordination Centre of the study by fax.

### Sample size

The Required number of subjects is estimated on the primary endpoint: disability progression at 2 years. From the following hypothesis:Frequency of disability progression at 2 years = 40%Relative risk of rapid disability progression at 2 years related to global atrophy = 1.6Alpha risk (α) = 5%Statistical power (1- β) = 90%Two-tailed test

The Required number of subjects is 178. With an expected drop-out rate of 20%, the number of subjects to be included is estimated at 214 patients.

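### The 20% drop-out allowance is added to 178 rather than taken from those enrolled, so 214 leaves about 171 evaluable patients, a small shortfall

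*Protocol article*

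**What the plan says.** The Sample size section of the protocol article bases the calculation on disability progression at 2 years. Its inputs are a 40% frequency of progression, a relative risk of 1.6 related to global atrophy, a 5% alpha ("Two-tailed test") and 90% power. It concludes: "The Required number of subjects is 178". The next sentence makes the allowance for loss: "With an expected drop-out rate of 20%, the number of subjects to be included is estimated at 214 patients".

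The Study design section uses the same figure as the number entering the study: "Multicentre and prospective cohort study with 214 patients enrolled". The Methods paragraph of the abstract also gives 214 as the number to be recruited. So 214 is the count before drop-out and 178 the count needed after it. The article nowhere defines the 20% as anything other than an ordinary drop-out rate.

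**The concern.** Three figures are stated together: 214 enrolled, 20% lost, 178 required. They cannot all hold, because 20% of 214 is 42.8 and removing that many leaves about 171. The pattern suggests that the allowance was computed as 20% of the required number and added on, whereas a drop-out rate acts on the patients who enter.

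What is at stake is whether the enrolment target delivers the evaluable number that the section itself asks for, and so whether the stated 90% power goes with that target. On the reading that reproduces 178, that number only just reaches 90%, so there is no slack to absorb a shortfall.

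**Working it through.** **Inputs** (all from Sample size): required number 178; drop-out 20%; number to include 214; progression frequency 40%; relative risk 1.6; two-sided alpha 5%; power 90%.

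**Step 1. Reproduce 178.** This needs two assumptions that the article does not state: 40% is the rate in patients without global atrophy, and the two atrophy groups are of equal size. Then p1 = 0.40, p2 = 0.40 × 1.6 = 0.64, and the mean is 0.52. The usual formula for two proportions (pooled variance under the null, no continuity correction) is

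n per group = [1.960 × √(2 × 0.52 × 0.48) + 1.2816 × √(0.40 × 0.60 + 0.64 × 0.36)]² / (0.64 − 0.40)²

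= [1.960 × 0.7065 + 1.2816 × 0.6859]² / 0.0576 = (1.3848 + 0.8790)² / 0.0576 ≈ 88.97, so 89.

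Total 2 × 89 = 178, as stated.

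**Step 2. Reproduce 214.** 178 × (1 + 0.20) = 213.6, so 214. The plan's figure is matched by this route.

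**Step 3. Inflate for a loss from those enrolled.** 178 / (1 − 0.20) = 222.5, so 223. Check: 223 × 0.80 = 178.4, which meets 178. The difference from the plan is 223 − 214 = 9 patients.

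**Step 4. What 214 delivers.** 214 × 0.80 = 171.2, so about 171. The shortfall is 178 − 171 = 7 patients.

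**Step 5. The drop-out that 214 can absorb.** 1 − 178/214 = 0.168, that is 16.8%, or 36 patients lost (214 − 36 = 178).

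**Step 6. Power**, under the two assumptions of step 1, with z = (0.24 × √n − 1.3848) / 0.6859 and n per group:

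| Evaluable | n per group | z | Power |
|---|---|---|---|
| 178 | 89 | 1.282 | 90.0% |
| 171 | 85.5 | 1.217 | 88.8% |

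The loss is about 1.2 percentage points.

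Steps 2 to 5 use only 178, 20% and 214. They do not depend on how 178 was obtained. Only step 6 needs the two assumptions.

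**The case against.** The best case for leaving the text alone is that the effect is too small to matter. Power of 88.8% against 90.0% changes no objective, endpoint or analysis, and the uncertainty in the assumed 40% and 1.6 is a larger matter than nine patients. This stands, and it is why the point is graded minor. It does not make the sentence true.

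A second argument is that 171 need not be the analysis set. The analysis section for the principal objective includes a mixed regression model for the change in score from inclusion to 2 years, and Table 1 schedules the DAD at baseline and at months 6, 12, 18 and 24. A patient who leaves after a post-baseline visit can still contribute. This also stands as a limit on the practical consequence. However, the sample size is set on 2-year progression, and the article does not appeal to the mixed model to justify 214.

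A reader might infer a much larger loss of power. The article writes "Frequency of disability progression at 2 years = 40" per cent without saying in which patients. If 40% is the frequency in the whole cohort, with equal groups, the two rates are about 30.8% and 49.2%. On that reading 178 evaluable patients would themselves give only about 71.4% power, and going from 178 to 171 would cost about 1.8 points more. The large gap would come from what the 40% means, which is a separate question, and it must not be charged to the drop-out step.

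A reader might also infer that recruitment has to rise to 223. The arithmetic does not require this. It requires only that the enrolment, the drop-out and the evaluable number agree.

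**Conclusion.** The point holds as a minor arithmetic error. Under the plan's own 20% drop-out, 214 enrolled leaves about 171 patients, 7 fewer than the 178 required. Keeping 178 would take 223, and 214 is enough only up to 16.8% drop-out. These counts are certain given the stated figures and the ordinary meaning of a drop-out rate.

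The power consequence, 90.0% to about 88.8%, is conditional. It rests on 40% being the rate without global atrophy and on equal atrophy groups. Both are inferred because they reproduce 178, and neither is stated. It also treats everyone who drops out as lost to the 2-year comparison. The documents do not support calling the study materially underpowered because of this step.

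**What to change.** Correct the sentence in Sample size in one of two ways:

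- State that 214 patients included with 20% drop-out gives about 171 evaluable patients and about 89% power, assuming that 40% is the 2-year progression rate in patients without global atrophy and that the groups with and without atrophy are of equal size. Both assumptions should be written out, because the power figure means nothing without them.
- Or state that 214 patients included provides 178 evaluable patients if drop-out does not exceed 16.8%.

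Either costs one sentence. The first also lowers the stated power slightly. Recruitment, the Study design section and the abstract can stay at 214. If the sponsor prefers to keep both 178 evaluable and 20% drop-out, the consistent target is 223, which is 9 more patients and means changing 214 wherever it appears.
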